### Timeline

Baseline survey collection started on 1 December 2017 and will be finished by July 2020. The home-visits team was trained in November 2017 and visits were launched shortly after initiation of baseline in the phase-1 home-visiting areas; the first births within this group occurred in February 2018. Due to logistical challenges, center-based programs were started later; the two areas randomly selected for phase 1 of the project were formally launched in July 2018. Phase 2 (both for home visits and center-based programs) was started in July 2019, with 10 neighborhoods added to the home-visiting programs, and eight added to the center-based programs.

Endline surveys are scheduled to start in April 2020 and will target children at age 2 years. With the targeted sample size of 3000 households we anticipate to complete endline by July 2021. BSID-III assessments will start in July 2020 and should be completed within 6 months.

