In this project, we assess the scalability of a locally adapted version of an early childhood program previously developed in Jamaica. Between 2014 and 2016, the Jamaican “Reach Up and Learn” curriculum was adapted to the Brazilian context and tested through a small randomized trial in São Paulo (ClinicalTrials.gov, ID: NCT0270400). The content, delivered through fortnightly home visits, comprises parenting-skill tips as well as child stimulation activities supported with basic toys, addressing motor, social emotional, and cognitive development and language for families with children aged from 9 to 36 months.

While the reach of this program was not universal in this original trial, the estimated impact on participating mothers was large, and the program was well received at the local level (manuscript with main results under review). While this curriculum was delivered through home visits in the original study in São Paulo, recent evidence from Bangladesh [6] suggests that similarly positive impacts can be achieved through center-based parenting groups that are substantially cheaper from a logistical perspective.

Given this and given also that the municipality had previously invested in a center-based model, it was decided to test both delivery platforms within this project. Given the relatively high burden of neonatal mortality in the study area, we also decided to start the intervention earlier. By enrolling pregnant women at the beginning of their third trimester, the revised intervention program aims to improve support for mothers during the antenatal and neonatal periods with the ambition to increase health service utilization and reduce the risk of adverse birth outcomes. Figure 1 presents the theory of change through which the curriculum may improve child survival and development.

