### Trial design

The study was designed as a stepped-wedge, cluster randomized controlled trial with three arms. Arm 1 represents intervention delivered through fortnightly home visits; Arm 2 consists of the same content delivered through fortnightly center-based group meetings; Arm 3 is the control group.

To avoid contamination, neighborhoods were used as units of randomization. All 53 neighborhoods in Boa Vista were classified according to the municipality vulnerability criteria. Only neighborhoods classified as B (medium vulnerability) and C (high vulnerability) will be targeted by the program. As of 2017, 42 neighborhoods were in this category.

Three neighborhoods had either existing home-visiting programs or other planned interventions, and were excluded from the study, leaving a final study sample of 39 neighborhoods. Figure 2 presents the neighborhoods vulnerability distribution.

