### Outcomes

The primary study outcome is child development at age 2 years as assessed by the PRIDI Scale. The secondary study outcome is child survival, which will be assessed using data from the municipality’s vital registration system (SIM and SINASC). Maternal depression will be assessed using the Center for Epidemiologic Studies Depression Scale (CES-D Scale).

Intention-to-treat analysis will be used to compare outcomes across the three study arms.

Additional per-protocol analysis will be conducted using data on program compliance. Our primary measure of compliance in the home-visiting arm will be the number of home visits completed. Our primary compliance measure in the center-based groups will be the number of sessions attended by the mother. Table 1 presents the data collection overview.

**Table 1 Tab1:** Data collection overview

Data collection phase	Instruments
Baseline (12,000)	Participant identification, anthropometrics, and habits Socioeconomic characteristics Household characterisits Previous gestational information Maternal depression (EPDS) Neighborhood characteristics and social support Couples’ conflict Parental knowledge Maternal cognitive development (WAIS) Paternal characteristics
Main endline (*N* = 3000)	Child development (PRIDI) – Primary outcome Maternal depression (CES-D) Caregiver self efficacy (PSOC) Parental style (ACT) Parental knowledge Child anthropometrics (height and weight)
In-depth endline assessment (*N* = 240)	Attachment and caregiver interactions (OMCI) Bayley Scales for Infant and Toddler Development (BSID-III)
Qualitative interviews	Focus groups with child development agents and group-meeting facilitators Individual interviews with program beneficiaries divided by full compliers, non-compliers, and dropouts by intervention study arm

*ACT*, *BSID-III* Bayley’s Scales for Infant and Toddler Development, *CES-D* Center for Epidemiologic Studies Depression Scale, *EPDS* Edinburgh Postnatal Depression Scale, *OMCI* Observation of Mother-child interaction, *PRIDI* Regional Project on Child Development Indicators, *PSOC* Parenting Sense of Competence Scale, *WAIS* Weschsler Adult Intelligence Scale

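### The PRIDI endline closes before children enrolled in pregnancy in phase 2 turn 2, and the protocol does not fix how phase-2 areas count in the ITT analysis

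*Protocol article*

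**What the plan says.** Trial design: "The study was designed as a stepped-wedge, cluster randomized controlled trial with three arms". The Objectives describe a rollout reaching about one third of communities in phase 1, two thirds in phase 2 and all in the last phase.

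The dates are in the Timeline. Home visits began shortly after baseline opened on 1 December 2017, and "the first births within this group occurred in February 2018". For the center arm, "the two areas randomly selected for phase 1 of the project were formally launched in July 2018". Then "Phase 2 (both for home visits and center-based programs) was started in July 2019", adding 10 home and 8 center areas. For the primary outcome, "Endline surveys are scheduled to start in April 2020 and will target children at age 2 years", and "With the targeted sample size of 3000 households we anticipate to complete endline by July 2021". Baseline interviews continue to July 2020. The Background sets the point of entry: "By enrolling pregnant women at the beginning of their third trimester".

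On analysis, Outcomes says: "Intention-to-treat analysis will be used to compare outcomes across the three study arms". Statistical methods adds only standard regression models. Sample size and power calculations draws the 3000 endline dyads at random from about 12,000 baselines. It sets 11 phase-1 areas of 120 households against 28 control areas of 60, with an intra-class correlation of 0.02.

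Eligibility criteria also admits women with a child under 1 year. Recruitment plans a small sample of them to study reduced exposure. Under Interventions, the child module runs from 2 to 36 months.

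**The concern.** A stepped wedge informs an outcome only if that outcome is measured in people exposed after the step. Here the second step and the endline window hardly overlap for children reached in pregnancy, which is how the program is meant to begin. The step also carries 8 of the 10 center areas allocated by then. Without it, the center effect on PRIDI rests on two neighborhoods.

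Three things follow. The design label promises information that the primary outcome cannot deliver. The stated sampling frame includes children who cannot be assessed. And 18 of 39 areas change arm during the study, while the ITT sentence names arms without a date. The two possible classifications give different estimands, and both pull the estimate toward no effect. Separately, the two phase-1 arms did not start together, so the earliest endline birth months differ in exposure between home and center areas.

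**Working it through.** **The plan's own figure.** Inputs from Sample size and power calculations: 0.25 SD, intra-class correlation 0.02, 120 and 60 households per area. Two-sided alpha 0.05 is my assumption, as none is stated.
- Total: 11×120 + 28×60 = 1320 + 1680 = 3000, as stated. Since 28 = 39 − 11, the controls include the 18 phase-2 areas.
- Effective n = k·m / (1 + (m − 1)×0.02). Control: 1680/2.18 = 770.6. Home: 1080/3.38 = 319.5. Center: 240/3.38 = 71.0.
- Power = Φ(0.25/SE − 1.96), with SE = √(1/n₁ + 1/n₀). Home: SE 0.0665, power 0.96. Center: SE 0.124, power 0.52.

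The stated 0.9 for each arm is therefore not reproduced for center with its two phase-1 areas, even before any dilution.

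**Calendar.**
- Age 2 between April 2020 and July 2021 means births from April 2018 to July 2019, which is 16 birth months.
- Enrollment in July 2019 about three months before birth gives birth about October 2019 and age 2 about October 2021. Only a woman enrolled in the month she delivers (July 2019) has a child at the edge of the window.
- Partial exposure: children born July 2018 to June 2019 (12 of the 16 months) were under 1 when phase 2 opened. They could join postnatally and still be assessed.

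**Sampling frame.** Baseline runs December 2017 to July 2020, which is 32 months. With enrollment at the start of the third trimester, April 2019 is the last month whose children turn 2 by July 2021. So at most 17 months are usable and 15 of 32 (47%) are too late. Under even accrual (an assumption) that is 12,000×15/32 = 5,625 baselines from which no endline child can be drawn.

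**Classification A: phase-2 areas as control (the sample size section).** They hold 18×60 = 1080 of 1680 control children. If births are even, at most 1080×12/16 = 810 (48%) were young enough to join after July 2019. The planned number is only a small sample and is not given. If a joining child gets half of the 0.25 SD (an assumption), the contrast falls by 0.0125 SD for every 10% of controls who join. At the 48% ceiling it falls by 0.06 SD, to about 0.19 SD.

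**Classification B: areas coded by final arm.** Assumptions: 120 households in phase-1 areas, 60 elsewhere, 10 areas left as control (effective n 600/2.18 = 275.2) and zero effect in phase-2 children.
- Home: 1080 of 1680 children (64%) come from phase-1 areas. Effect 0.25×1080/1680 = 0.161. Variance (1080×3.38 + 600×2.18)/1680² + 1/275.2 = 0.00539, SE 0.0734, power Φ(2.19 − 1.96) = 0.59.
- Center: 240 of 720 (33%). Effect 0.25×240/720 = 0.083. Variance (240×3.38 + 480×2.18)/720² + 1/275.2 = 0.00722, SE 0.0849, power Φ(0.98 − 1.96) = 0.16.
- With half the effect in phase-2 children instead of none: home 0.205 SD, power 0.80; center 0.167 SD, power 0.50.

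**Center against home in phase 1.** With a July 2018 center launch, 3 of the 16 birth months (April to June 2018) precede launch. Six (April to September 2018) precede a full third-trimester start. Home areas had births under the program from February 2018.

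**The case against.** The strongest reply is that the sample size section already treats the PRIDI comparison as phase 1 against 28 controls, so the protocol leans to Classification A. That stands. A reader might infer that the plan counts unexposed children as treated; the documents do not say so. The losses under Classification B are conditional on a coding that is not stated, and they are a worst case. Under the plan's own count the risk is the reverse: partly treated children among the controls.

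A reader might also infer that phase 2 adds no exposed children at all. That is too strong. Postnatal entry is allowed, the child module runs to 36 months, and most of the endline birth cohort was under 1 in July 2019. Likewise, center children born April to June 2018 were about 0 to 3 months old at launch. They missed antenatal content and some or all of the neonatal content, not the program, and analyzing them as randomized is ordinary ITT.

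Nor are the later baselines wasted. They are screening interviews that also establish program eligibility, and the mortality outcome links vital registration to the rollout, so phase-2 births can inform it.

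Finally, details of exposure coding often sit in an analysis plan, which is not shown. That does not dispose of the point. The design label, the ITT sentence, the sampling rule and the Timeline are all stated in this article and do not fit together.

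**Conclusion.** The point holds in this form. On the protocol's own dates, the second step adds essentially no child exposed from pregnancy to the primary outcome, and PRIDI is in effect a parallel comparison of 9 home and 2 center areas with areas not yet treated. The random draw from all 12,000 baselines cannot be carried out as described, because about 47% of baseline months come too late. The ITT classification of the 18 phase-2 areas is open, and either choice dilutes the contrast: by an amount that depends on the unstated number of postnatal joiners if they are controls, or down to 0.16 SD (home) and 0.08 SD (center) in the worst case if coded by final arm.

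This rests on entry about three months before birth, assessment close to the second birthday (no age tolerance is given; about three months' leeway before it would admit the first phase-2 children), even accrual for the shares, and two-sided alpha 0.05. The count of 18 comes from the Abstract and Timeline. Randomization gives 27 treated areas in phase 2 where 11 + 18 = 29, so those figures need reconciling too.

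It is tempting to conclude that the endline should simply run longer. The documents do not support that: phase 3 brings the remaining 10 control areas into the program on a date that is not given, so a later endline could lose its comparison group.

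**What to change.** - State that the primary PRIDI analysis compares phase-1 areas with areas not yet treated, and align the stepped-wedge description with this.
- Fix the ITT classification by neighborhood and birth date relative to that area's launch in its randomized arm, and say how phase-2 children enrolled postnatally are handled.
- Restrict the endline sampling frame to births that reach age 2 within the window.
- Compare each arm with controls of the same birth months, and add a sensitivity analysis limited to center-arm births from about October 2018.
- Make no claim that the second step informs PRIDI unless the endline window and the phase-2 and phase-3 start dates are reconciled.

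The cost is wording and a revised sampling list. Trial status is given as of November 2019, before the scheduled start of endline, so both were still open to change. The price in the sensitivity analysis is fewer usable births in an arm that already has only two areas: 10 of the 16 birth months remain (October 2018 to July 2019).

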### Data management

Baseline and endline data will be collected in electronic format on tablets and stored on a secure server. The project leader will be responsible for the anonymization of the data system. A unique identifier will be used in the data system to preserve participant privacy and confidentiality.

### Statistical methods

For statistical analysis, standard regression models will be used for the continuous PRIDI outcome. Logistic regression models will be used for the secondary outcome of child mortality. All analysis will be conducted using the Stata 15 statistical software package. Primary analysis will be intention-to-treat. To assess the impact of partial compliance, we will also estimate average treatment effects on the treated (per-protocol analysis).

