### Sample size and power calculations

Based on the estimated number of births in the targeted B and C areas, we anticipate completing approximately 12,000 baselines (screening interviews) over the project period. Out of these mother-child dyads, we will randomly select 3000 for the endline assessment. We assume an average causal effect of 0.5 standard deviations (SD) for compliant mothers. With an anticipated average compliance rate of 50%, the study is powered to detect an intention-to-treat effect of 0.25 SD with power 0.9 between each of the two intervention arms and the control arm, assuming an average sample of 120 households in each of the 11 neighborhoods treated in phase 1, and an average sample of 60 households in each of the 28 control neighborhoods, assuming an intra-class correlation of 0.02.

In order to assess spillovers within households, we will also assess all older siblings under age 4 years in households selected for endline. Based on the high fertility rates observed at baseline, we anticipate a sample of 750 older siblings. Assuming a uniform distribution of siblings across clusters, the study is powered to detect a 0.3-SD change in PRIDI score with power 0.8.

In order to assess domain-specific changes in children’s development, we will also invite 80 mothers from each arm for a detailed assessment using Bayley’s Scales for Infant and Toddler Development (BSID-III). For these assessments, we will randomly select mothers from the control group as well as compliant mothers from the two intervention arms.

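### The effect on the treated is labeled a per-protocol analysis based on visits or sessions completed; the two are different estimands, and a contrast by attendance is not protected by randomization

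*Protocol article*

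**What the plan says.** Under Statistical methods, the protocol article states that "Primary analysis will be intention-to-treat". To deal with partial compliance it adds that "we will also estimate average treatment effects on the treated (per-protocol analysis"), so the parenthesis presents the two terms as one analysis.

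The Outcomes section uses the same label: "Additional per-protocol analysis will be conducted using data on program compliance". It then gives one measure per arm. For home visits, "Our primary measure of compliance in the home-visiting arm will be the number of home visits completed". For groups, "Our primary compliance measure in the center-based groups will be the number of sessions attended by the mother". Neither section gives a compliance threshold, a comparison group or an estimator that uses the random assignment. The methods named are standard regression for PRIDI and logistic regression for mortality.

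The sample size section treats compliance differently. It begins "We assume an average causal effect of 0.5 standard deviations (SD) for compliant mothers", continues "With an anticipated average compliance rate of 50" percent, and concludes that "the study is powered to detect an intention-to-treat effect of 0.25 SD with power 0.9 between each of the two intervention arms and the control".

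**The concern.** The effect on the treated is a causal quantity. If control mothers have no access to the program, and assignment acts on the child only through participation, it equals the ITT effect divided by the compliance rate, and randomization protects it. A per-protocol analysis selects or classifies mothers by what they did after randomization. Mothers who keep up fortnightly visits may differ from those who do not in ways that also predict child development, so such a contrast mixes program effect with selection.

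The article uses both names for one analysis, and an analyst who follows the per-protocol label literally would condition on attendance. With half of mothers expected not to comply, this is the natural estimate of what the program does for families who take part, so it matters which quantity is produced.

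Raw counts add a smaller difficulty, because they partly reflect what was offered. The neonatal module has three visits at home but one or two sessions at the centers. Home visits began shortly after baseline collection opened in December 2017, the phase 1 centers in July 2018, and phase 2 in July 2019.

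**Working it through.** **Inputs from the protocol article.** Sample size section: effect in compliant mothers 0.5 SD; compliance c = 0.50; ITT effect 0.25 SD; 120 households in each of 11 phase 1 neighborhoods; 60 in each of 28 control neighborhoods; intra-class correlation 0.02. Randomization section: the 11 are nine home-visit and two center neighborhoods.

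**Assumed input.** d, the mean untreated PRIDI score of compliers minus that of non-compliers, in SD. The documents give neither its size nor its sign.

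**Step 1: the plan's own figure.** ITT = complier effect x c = 0.5 x 0.50 = 0.25 SD, which reproduces the stated value. Reversed, 0.25 / 0.50 = 0.50 SD. This is the Wald (instrumental-variable) relation, and it holds whatever d is.

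**Step 2: a contrast by attendance.** Suppose compliers in a treated arm were compared with all controls. Controls are a mixture of would-be compliers (share c) and would-be non-compliers (share 1 - c). Therefore

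contrast = complier effect + (1 - c) x d, and bias = (1 - c) x d.

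| Compliance | d = -0.3 | d = -0.1 | d = 0 | d = +0.1 | d = +0.3 |
|---|---|---|---|---|---|
| 30% | -0.21 | -0.07 | 0 | +0.07 | +0.21 |
| 50% | -0.15 | -0.05 | 0 | +0.05 | +0.15 |
| 70% | -0.09 | -0.03 | 0 | +0.03 | +0.09 |

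At the planned 50%, a true 0.50 SD would be estimated as anything from 0.35 to 0.65 SD over this range of d.

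**Step 3: simulation.** With 2,000,000 units, c = 0.5, effect 0.5 SD and d = +0.3, the ITT estimate was 0.251, the Wald estimate 0.501 and compliers against all controls 0.651. The formulas give 0.25, 0.50 and 0.65.

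**Step 4: precision of the instrumental-variable estimate.** With k clusters of m households, the variance of an arm mean is [1 + (m - 1) x 0.02] / (k x m), in SD units.

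- Control, 28 x 60: 2.18 / 1680 = 0.00130.
- Home visits, 9 x 120: 3.38 / 1080 = 0.00313. ITT SE = sqrt(0.00313 + 0.00130) = 0.0665.
- Centers, 2 x 120: 3.38 / 240 = 0.01408. ITT SE = sqrt(0.01408 + 0.00130) = 0.124.

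Treating c as known, the SE of the complier effect is the ITT SE / 0.5: 0.133 for home visits and 0.248 for centers. For a true 0.5 SD, z is about 3.8 and 2.0, the same as the ITT analysis gives for 0.25 SD.

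**The case against.** The strongest reply is that only a word is wrong. The Statistical methods section names the effect on the treated as its target, and the sample size arithmetic is the instrumental-variable relation. The counts could serve as the exposure in such a model. The analysis is secondary, and a journal article may leave its estimator to a fuller document.

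Much of this stands:

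- A reader might infer that the plan compares self-selected compliers with all controls on PRIDI and is therefore biased. No section specifies that comparison for PRIDI or mortality. Only the Bayley sub-study draws compliant intervention mothers alongside randomly selected controls, and that is a separate assessment.
- A reader might also infer that the bias flatters the program. The sign of d is unknown: the population is selected for vulnerability, and the article does not say whether better-placed or needier mothers attend more.
- Nor does the article say that this estimate feeds the cost-effectiveness analysis. Cost-effectiveness is listed as an objective without naming the effect estimate to be used.
- Unequal numbers of sessions offered do not in themselves bias a comparison of one arm with control, and no comparison of counts between arms is planned.

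What does not stand is the defense that this is merely missing detail. The text positively equates two different analyses, repeats the per-protocol label in a second section, and nowhere names a method based on the randomization.

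**Conclusion.** The point holds as a conflation of estimands with a conditional consequence. The article equates the effect on the treated with a per-protocol analysis by attendance. Taken literally, that label need not recover the 0.5 SD complier effect on which the trial was sized. If carried out as compliers against all controls, the bias is (1 - compliance) x d: between -0.15 and +0.15 SD at 50% compliance for an assumed d of -0.3 to +0.3 SD, and zero only if attendance is unrelated to prognosis. The range of d is illustrative and does not come from the documents. The primary ITT analysis is unaffected, so this is a worthwhile correction to a secondary analysis and no threat to the main result.

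**What to change.** Replace the per-protocol label in both sections with a complier effect estimated by two-stage least squares, separately for each arm against control. The instrument is the randomized neighborhood assignment together with rollout phase. Include birth-month effects and use the same cluster-level inference as the ITT model.

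Define participation in advance, in one of two ways:

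- Binary compliance, which matches the 0.5 x 50% assumption. Mothers who attend some sessions but fall below the threshold count as untreated, which strains the exclusion restriction if they benefit.
- The proportion of offered visits or sessions attended, which allows for unequal numbers offered. The result is then the effect of full attendance and should be reported as such; it is not the same quantity as the binary complier effect.

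Count later enrolment as participation. Women with children under 1 year may enroll and phase 2 opened in July 2019, so children born under control in phase 2 areas from about July 2018 could still take part. If they do, controls have some access and the estimate is no longer simply the effect on the treated.

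Present any dose-response by visit count as descriptive only.

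The cost is a few sentences and a standard command in Stata, which the article already specifies. The interval is about twice as wide as the ITT interval. With an SE of about 0.13, the home-visit estimate remains informative. With an SE of about 0.25 from two phase 1 clusters, the center estimate is weak, and inference on so few clusters is fragile. Validity rests on the exclusion restriction: assignment must have no effect on children whose mothers do not take part.
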